**Study design.**

### Participants

#### Selection criteria

Individuals who meet the inclusion criteria will be recruited. The criteria are: (1) aged 18 years or above; (2) have smoke at least one cigarette per day in the past 30 days; (3) not currently undergoing any other smoking cessation program; (4) able to communicate in Cantonese; (5) a Hong Kong resident; (6) currently residing in Hong Kong and expecting to continue for the next six months; and (7) have access to a telephone.

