#### Follow-up assessments

At three and six months, the participants will be re-contacted by telephone to complete the follow-up assessments assessing their smoking status, attempts to quit, and ability to deal with physical sensations, emotions, and thoughts without smoking. The assessments will be conducted by trained research assistants who are blind to the treatment condition. Participants who self-report as quitters at the six-month follow-up interview will be invited to perform the CO test in the clinic. Participants in the ACT group will also need to complete an evaluation survey through telephone at the six-month follow up session.

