### Intervention

#### ACT

In addition to the self-help materials on smoking cessation given to the participants in both groups, the participants randomized to the ACT condition will be offered an initial individual face-to-face ACT session at the clinic and two telephone follow-up sessions at one week and one month following the initial session of ACT intervention. Each session will be around 15 to 20 minutes, for a total of approximately one hour over the three sessions. The sessions will be delivered by a counselor experienced in delivering ACT. The intervention will be based on a treatment protocol developed in this study, which is guided by previous ACT for smoking cessation protocols [19] and will incorporate all six core processes of ACT. The first session will mainly help the participants to: (1) accept their cravings and withdrawal symptoms as well as to develop skills for dealing with them without smoking, and (2) identify the values involved in quitting and develop a plan to stop smoking at the initial ACT intervention session. Subsequent sessions will include reinforcing the plan that was developed to quit smoking, supporting participants in continued actions to quit, guided by those identified values, and reinforcing the message on the value of quitting. ACT metaphors/exercises will be used throughout the three sessions. Table 1 provides a session-by-session outline of the intervention.

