### Measures

#### Questionnaires

A structured questionnaire will be completed by participants at the baseline, three-month, and six-month follow-up sessions. Demographic data, including age, gender, educational level, current occupation, marital status, and number of people in the household will be recorded at baseline. The questionnaires include questions related to tobacco consumption, such as the number of cigarettes smoked per day, smoking behaviors, withdrawal symptoms, previous attempts to quit, and experiences. The participants’ readiness to quit smoking at different time points will also be recorded [25]. The questionnaires will also include the following scales:

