#### Biochemical measures

The level of exhaled carbon monoxide (CO) will be measured for all participants at baseline by means of a micro smokerlyser CO monitor. Urinary cotinine assays will be collected and the exhaled CO test will again be performed at the six-month follow-up session for self-reported quitters. Breath CO and cotinine have been found to be sensitive methods of determining smoking status [31] and exposure to tobacco smoke [32,33]. Participants with exhaled CO levels of 6 ppm or above [34] or a NicAlert test at level three or above according to the manufacturer will be considered current smokers.

The primary outcome will be self-reported seven-day point prevalence abstinence at the six-month follow up, meaning no smoking at all in the past seven days preceding the six-month follow-up assessment. Secondary outcomes will include: (i) validation of the self-report of not smoking obtained by the CO measurement and urinary cotinine; (ii) readiness to quit smoking; (iii) average number of cigarettes consumed daily in the past seven days; (iv) number of attempts to quit in the past month; (v) self-report of not smoking in the past seven days; and (vi) household smoking status in the past month.

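### Counting quit attempts over the past month only, at three and six months, gives early sustained quitters the same zero as people who never tried

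*Protocol article*

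**What the plan says.** All places are in the protocol article.

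- **Outcome.** The list of secondary outcomes, at the end of Biochemical measures, includes "iv) number of attempts to quit in the past month".
- **Timing of assessment.** Follow-up assessments: "At three and six months, the participants will be re-contacted by telephone to complete the follow-up assessments".
- **Timing of treatment.** In the ACT section, the first session helps participants to "develop a plan to stop smoking at the initial ACT intervention session". It is followed by "two telephone follow-up sessions at one week and one month following the initial session of ACT intervention", and no later ACT contact is described.
- **Entry.** Participants must "have smoke at least one cigarette per day in the past 30 days", so nobody is an established abstainer at baseline.
- **Reading of results.** The Statistical analysis section takes a group-by-time interaction, with more change under ACT, as the main evidence of efficacy. It makes no exception for this outcome.

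Attempts are also mentioned without a recall period in Follow-up assessments and in Questionnaires ("withdrawal symptoms, previous attempts to quit, and experiences"). Neither place redefines the outcome.

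**The concern.** A quit-attempt outcome should show whether the intervention moved people to try. Here the recall period and the visit schedule miss each other: the push to quit comes in the first month, and the outcome looks at one month just before each much later call.

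Someone for whom the intervention worked at once has no attempt to report in either window. Someone who tries and fails repeatedly in the last month scores higher. The count thus mixes not trying with not needing to try again. If it is read by the rule in Statistical analysis, a real benefit could show as no difference, or as a small difference in the wrong direction, on this outcome.

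**Working it through.** The plan gives no expected figure for quit attempts, so there is none to reproduce. The total of 116 is used below only for scale.

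**1. Which months are observed.** A one-month look-back at three and six months covers about months 2–3 and 5–6, that is 2 of 6 months. ACT contact falls at session 1, one week and one month, which is month 0–1. The Design section can be read as timing follow-up from the end of the intervention. On that reading the windows move about a month later and still miss month 0–1.

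**2. Scores of three kinds of participant.**

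| Participant | Score at 3 months | Score at 6 months |
|---|---|---|
| Quits in month 0–1, stays abstinent | 0 | 0 |
| Never tries | 0 | 0 |
| Tries and relapses within a window | 1 or more | 1 or more |

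For the first row the change from baseline cannot be positive, because the follow-up count is zero and the baseline count is at least zero.

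**3. Size, under a simple model (assumption).** A share s quits in month 0–1 and stays quit. Everyone else makes attempts at a Poisson rate r per month, equal in both arms.

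Mean past-month attempts = (1 − s) × r, so the ACT/control ratio is (1 − s_ACT)/(1 − s_control), whatever r is.

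Inputs:
- s_control = 7.4%, the control quit rate in the Sample size section.
- s_ACT is not given in the document. Three assumed values are used:
  - 15.9%, from the Sample size section's g = 0.475 converted to an odds ratio: exp(0.475 × π/√3) = 2.37, applied to odds of 0.074/0.926.
  - 24.1%, from the same 0.475 read as Cohen's h.
  - 29%, the quit rate of the single-arm telephone study described in the Background.

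| s_ACT | Ratio | ACT mean lower by | Break-even |
|---|---|---|---|
| 15.9% | 0.841/0.926 = 0.91 | 9% | 1.10 |
| 24.1% | 0.759/0.926 = 0.82 | 18% | 1.22 |
| 29% | 0.710/0.926 = 0.77 | 23% | 1.30 |

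The break-even is 0.926/(1 − s_ACT): how many times as often the remaining ACT participants must try, relative to the remaining controls, for the deficit to vanish.

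**4. Scale against noise.** With r = 0.3 (assumption) and s_ACT = 24.1%, the means are 0.228 and 0.278, a difference of 0.05. The variance per person is (1 − s)(r + r²) − [(1 − s)r]², which gives 0.244 in ACT and 0.284 in control. With 58 per arm (116/2, equal allocation assumed) the standard error is √[(0.244 + 0.284)/58] = 0.095. The artefact is about half a standard error.

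**5. The alternative measure.** Any attempt since baseline has expectation s + (1 − s)(1 − e^(−6r)) over six months.

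| r | ACT at 15.9% / 24.1% / 29% | Control |
|---|---|---|
| 0.1 | 54% / 58% / 61% | 49% |
| 0.5 | 95.8% / 96.2% / 96.5% | 95.4% |

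The direction is now right, though there is little contrast when attempts are frequent. A mean count since baseline, s + (1 − s) × 6r, would not be enough. It rises with s only if 6r is below 1, and at r = 0.2 with s_ACT = 15.9% it is 1.168 against 1.185. The yes/no form is what helps.

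**The case against.** Several stronger readings are tempting, and the document does not support them.

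- **That the outcome must work against ACT.** The deficit needs similar attempt rates among non-quitters in both arms. Later ACT sessions are meant to support continued efforts to quit, so relapsers in that arm may try more often. A rate 1.10 to 1.30 times that of controls removes the deficit. This objection stands: the direction is expected, not certain.
- **That it would show apparent harm of some fixed size.** The 9% to 23% treats every abstainer as an early sustained quitter. The 7.4% is a point-prevalence rate and can include recent quitters and people who relapsed and quit again, who may score an attempt. The range is therefore an upper-end illustration, and half a standard error is unlikely by itself to look like harm.
- **That early attempts go unrecorded.** The questionnaire item on earlier attempts has no stated window and may capture them. What the text establishes is only that the listed outcome does not count them.
- **That "ii) readiness to quit smoking" is undefined for people who have quit.** The Questionnaires section cites an instrument for readiness that is not shown, and it may have a category for quitters. No point is made of it here.

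It can also be said that the scoring of abstainers belongs in an analysis plan. That is fair for the scoring rule. The recall period, however, is fixed in the article, and analysis alone cannot recover through this outcome an attempt in the first two months that ended in relapse.

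Finally, the primary outcome, self-reported abstinence among the secondary outcomes, and daily cigarette consumption all credit early sustained quitters correctly. This stands and limits the weight of the point.

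**Conclusion.** The point holds and is minor. As defined, the outcome leaves out the month in which the ACT quit plan is made and all sessions occur. It scores an early sustained quitter the same as someone who never tried, does not rise with success, and so cannot bear the reading that more change means efficacy.

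The scoring follows from the text alone. The size does not: 9% to 23% fewer mean attempts under ACT rests on equal attempt rates among the remaining participants, a 7.4% control share of sustained early quitters, and assumed ACT shares of 16% to 29%. One secondary outcome in a small feasibility trial is affected.

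**What to change.** 1. Keep the past-month item, so that it can still be compared with baseline, but do not read a larger change on it as evidence of efficacy.
2. Add one question at each follow-up call on attempts since the previous assessment (baseline to three months, three to six months).
3. Compare any quit attempt since randomisation between arms, counting anyone abstinent at follow-up as having made at least one.

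Limiting the count to continuing smokers is not a good substitute, because it compares groups selected after randomisation.

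The cost is one extra telephone question at each of two calls. There will be somewhat more recall error over three months than over one. The new item has no baseline value, so it must be analysed as a between-arm comparison and not as change from baseline.

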### Treatment feasibility

The feasibility of the ACT program will be assessed by investigating: (i) program acceptability as measured by the participants’ and facilitators’ perceptions of the program; (ii) participant recruitment; (iii) program attendance and retention; and (iv) the participants’ acceptance of physical cravings, emotions, and thoughts related to smoking, as well as their commitment to quit smoking.

### Treatment fidelity

Standardization in the delivery of the intervention will be enabled by employing a written manual for ACT. Treatment sessions will be audio-recorded and random samples of audio files (15-20%) will be rated by two trained independent assessors for treatment fidelity using The ACT Core Competency Rating form [28]. The intraclass correlation will be computed for ratings between the two assessors to ensure that the treatment fidelity ratings are reliable. Feedback on the outcome of these reviews will be provided to the research team and subsequently explored under weekly supervision.

### Statistical analysis

Statistical analyses will be carried out using the Statistical Package for Social Sciences (SPSS) Statistics v.21 software program. Statistical significance will be considered as p < .05. Descriptive statistics for basic demographics, number of sessions attended by the participants, intervention total length, and per-call duration will be computed. Baseline data will be analyzed to check the comparability of the intervention and control group. The primary analysis is differential changes in the ACT group versus the control group from the baseline to the three-month and six-month follow-up sessions, which will be analyzed within the framework of the Treatment Group. Analyses will be undertaken using mixed-model repeated measures. Primary evidence of the efficacy of ACT will be a significant two-way interaction demonstrating greater change in outcome measures in the ACT group from pre- to post-intervention. An intention-to-treat analysis will be performed. This approach is regarded as the most appropriate method of analyzing RCT data by the highest-quality journals, which have adopted the CONSORT standard [35].

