#### Sample size

Sample size calculations were based on the primary outcome of smoking cessation- 7-day point prevalence quit rate. As there has been no study that included a brief ACT for smoking cessation in HK, the sample size estimation was taken reference from available ACT studies for smoking cessation [17-20]. Their pooled effect size (Hedge’s g) was 0.475. The comparisons conditions for ACT in these studies included active treatment (e.g. Nicotine Replacement Therapy, Cognitive Behavioral Therapy); Bupropion; and self-help information with longest 12-month follow-up. According to a smoking cessation study conducted in Hong Kong [9], the 7-day point prevalence quit rate of the control group was 7.4% (i.e. receiving self-help materials). With a significance level of 5% and a power of 90%, under the principle of intention-to-treat analysis, 116 participants will be required for the study.

According to a previous smoking cessation study using a proactive approach [10], around 40% of the smokers who were approached completed the baseline interview on smoking patterns and that 45% of them accepted the invitation to participate in a proactive smoking cessation program. Given that attendance in the community services of the six targeted primary health care centers was 13,000 in the past year and that the prevalence of daily smokers was about 11.1% of the population in 2011 [24], it is estimated that recruiting participants from the six health care centers over a period of seven to eight months can support the required sample size of the study.

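### The stated primary analysis, a group-by-time interaction over three and six months on unnamed outcome measures, does not isolate the primary outcome, abstinence at six months

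*Protocol article*

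**What the plan says.** Three parts of the protocol article bear on the primary test.

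- **Outcome.** The end of the Biochemical measures section fixes one binary outcome at one time: "The primary outcome will be self-reported seven-day point prevalence abstinence at the six-month follow up". The Sample size section uses the same endpoint: "Sample size calculations were based on the primary outcome of smoking cessation- 7-day point prevalence quit rate".
- **Analysis.** The Statistical analysis section states: "The primary analysis is differential changes in the ACT group versus the control group from the baseline to the three-month and six-month follow-up sessions". It adds: "Analyses will be undertaken using mixed-model repeated measures". The success criterion is: "Primary evidence of the efficacy of ACT will be a significant two-way interaction demonstrating greater change in outcome measures in the ACT group". That sentence ends by referring to change from before to after the intervention, without saying which follow-up counts as after. The section names neither the quit rate nor a six-month comparison between arms, and gives no link function.
- **Baseline.** The Selection criteria require that participants "have smoke at least one cigarette per day in the past 30 days". Nobody can therefore be abstinent for seven days at entry, and the primary outcome is zero for everyone at baseline.

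**The concern.** The outcome called primary and the analysis called primary answer different questions. The first asks whether more ACT than control participants are abstinent at six months. The second asks whether the arms' profiles over three time points differ in any way, on measures that are not named.

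At stake is what a positive result would mean. A trial in which ACT raises quitting at three months and the gain is gone by six months could meet the stated criterion for efficacy with no effect on its own primary outcome. The plural wording also leaves open which measure has to show the interaction. The power statement, which concerns the quit rate, does not describe the interaction test.

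**Working it through.** **Inputs.** From the article: total sample size 116; control quit rate 7.4%; pooled effect size 0.475 ("Their pooled effect size (Hedge’s g) was 0.475"); significance at p < .05; assessments at baseline, three and six months. Assumed: equal allocation, so 116 / 2 = 58 per arm; latent correlation of 0.6 to 0.9 between three- and six-month abstinence; no missing data. The plan gives no figure for the interaction test to reproduce. The 116 is taken as given, and this point does not depend on how it was derived.

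**Step 1: what the interaction tests.** Degrees of freedom = (2 − 1) × (3 − 1) = 2. The null hypothesis is that the arms have the same change at three months and the same change at six months. A departure at either time counts against it.

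**Step 2: role of the zero baseline.** On the risk-difference scale the group-by-six-month contrast is (p6,ACT − 0) − (p6,control − 0) = p6,ACT − p6,control, which is the six-month risk difference. Illustration with 14/58 and 4/58 quitters: 0.241 − 0.069 = 0.172. The pooled proportion is 18/116 = 0.155, the standard error is √(0.155 × 0.845 × 2/58) = 0.067, z = 2.56 and p = 0.010. That contrast would test the primary outcome, but the section does not specify it.

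**Step 3: the same data with a logit link.** Baseline log-odds are log(0/58) in both arms, which is minus infinity, so a change in log-odds from baseline is undefined. Fitting 0/58 and 0/58 at baseline, 6/58 and 12/58 at three months, and 4/58 and 14/58 at six months (control, then ACT) gave interaction standard errors of about 24,000 and Wald p of about 1.0, against p = 0.010 in Step 2. This applies only if a logit link is used with the baseline row included.

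**Step 4: a transient effect.** The ACT rate of 24% is one conversion of the plan's effect size, by the arcsine scale: sin²(arcsin√0.074 + 0.475/2) = sin²(0.2755 + 0.2375) = 0.241. Other conversions give 15.9% to 19.8%. Abstinence was simulated with 58 per arm and baseline fixed at zero, in 4,000 to 6,000 trials per scenario. The interaction was the split-plot (compound-symmetry) F test. Where two percentages appear, they are for correlations 0.6 and 0.9.

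| Scenario (ACT vs control) | Interaction p < .05 | Six-month comparison p < .05 |
|---|---|---|
| 7.4% vs 7.4% throughout | 5.2%, 5.0% | about 5% |
| 24% vs 7.4% at three months, equal at six | 75%, 83% | about 5% |
| Equal at three months, 24% vs 7.4% at six | 75%, 83% | 72% |
| 24% vs 7.4% at both | 73%, 77% | 73%, 72% |

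In the second scenario the baseline-to-six-month contrast from the same model was significant in only 1% to 2% of trials. The false signal therefore comes from the omnibus test, not from the zero baseline.

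**Step 5: sensitivity.** With 30% against 7.4% at three months only (also assumed), correlations of 0.5 and 0.8, and either an unstructured covariance or compound symmetry, the interaction was significant in 86% to 95% of trials and the six-month comparison again in about 5%.

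**The case against.** The strongest reply is that a repeated-measures model can target this outcome. That is right. A reader might infer from the all-zero baseline that change from baseline carries no information; Step 2 shows the opposite. A reader might also infer that a linear model on binary data breaks down. In these simulations the interaction kept its size near 5%, and with the split-plot test it lost no power for a six-month or sustained effect.

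The logit failure in Step 3 depends on a link the article does not name. It is a risk to avoid, not an error in the text.

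A reader might further infer that any one of seven listed outcomes could count, giving 1 − 0.95⁷ = 30% false positives. The article does not support that. It designates one primary outcome. Of the six secondary items, one repeats seven-day self-reported abstinence and another is biochemical validation of it, done at six months in self-reported quitters only. Even five distinct outcomes would give 1 − 0.95⁵ = 23% only if they were independent, which is implausible here.

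It can also be said that contrasts and links belong in an analysis plan, that before-to-after change could be read as a single contrast, and that this is a small trial of feasibility and potential efficacy. The first is fair for technical detail. But the section itself states a primary analysis and a criterion for efficacy, and the preceding sentence names both follow-ups. The article also claims 90% power for the quit rate, so the efficacy test has to match it.

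**Conclusion.** Wrong as written. The Statistical analysis section conflicts with the outcome definition and the Sample size section on what the trial's primary test is. The stated interaction isolates neither six-month abstinence nor the six-month time point, and can be met by a three-month effect alone: 75% to 83% of simulated trials, against about 5% for a six-month comparison.

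Those percentages rest on 58 per arm, the assumed correlations and an assumed complete loss of a 24% against 7.4% effect by six months. The article predicts no such pattern. The figures show what the criterion permits, not what is likely. The conflict between the sections needs no assumption.

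The finding does not extend to saying that the mixed model cannot test the primary outcome, or that its type I error is inflated when there is no effect at any time.

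**What to change.** In the Statistical analysis section, state that the primary analysis is a single between-arm comparison of the proportion with self-reported seven-day abstinence at six months, among all randomised participants, reported as a risk difference with a 95% confidence interval and a two-sided 5% test. Tie primary evidence of efficacy to that test alone.

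Keep the group-by-time mixed model as supportive, for secondary measures that vary at baseline, such as cigarettes per day, the AAQ-II and the ERQ. Report three-month abstinence as a secondary outcome.

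The cost is a few reworded sentences. The analysis becomes simpler, and no additional data or assessments are needed.
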